### 9.5.2 Immunogenicity variables

IFN- $\gamma$  Elispot responses will be measured using freshly isolated PBMCs which will be purified from whole blood. Cells will be stimulated using pools of peptides derived from the vaccine and also negative and positive control stimuli. The number of spot-forming cells (SFC), indicative of IFN- $\gamma$  cytokine release will be enumerated using an automated Elispot reader. A positive result will be defined as numbers of spot-forming cells (SFC) more than four times the background (RPMI medium only) and > 55 SFC per million PBMC (Merck definition).

The proportion of CD4+ and CD8+ T-cells producing particular cytokines/chemokines and expressing cytolytic markers in response to HIV-1 peptides (as used in the Elispot assay) will be assessed. Frozen PBMCs will be used and thawed prior to analysis according to established methods. PBMCs will be stimulated *in vitro* and T-cell subsets and cytokine responses described using multi-parameter flow cytometry. Subsets of T-cells will be identified on the basis of the expression of cell surface markers and the percentages of CD4+ and CD8+ T-cells producing cytokines/chemokines will be determined with reference to the responses to control stimuli.

Binding antibodies with specificity for HIV antigens (Clade A, C and E) including those specific for the immunogen CN54rgp140 will be measured using standard ELISAs. ELISA absorbance readings for binding antibodies will be classified as 'response' or 'no response' using pre-defined cut-offs. Only samples with a detectable antibody response will be subjected to endpoint titration. In cases when a sample is positive for the presence of binding antibodies to CN54rgp140, the absolute concentration of antibody will also be determined. The concentration will be calculated relative to a commercially available standard purified antibody which will be titrated on the same plate as sample sera. Assays for the detection of neutralizing antibodies to HIV subtypes A, C and E will be performed using standardised assays including those using the TZMBL cell line and PBMCs.

All the immunogenicity endpoints will be signed off by the Laboratory Investigators. In the unlikely event that the Laboratory Investigators cannot reach consensus on a response, an expert Endpoint Panel will be assembled to make a final decision.

Prior to the main analysis, the Statistical Analysis Plan will be finalised describing the methods for comparing the groups in detail. The decision to compare the proportion of responders, or the magnitude of response, and the definition for these parameters will be informed by the full analysis of TaMoVac 01 and the results of other relevant clinical trials, with the aim of defining a 'clinically meaningful result'. Proportions will be presented with a confidence interval and groups compared using Fisher's exact test. Response magnitude will be compared between groups using rank tests.

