### **1.1.5 Duration**

The enrolment period is planned to be 10 months. Study participants will be monitored through week 12 (optionally week 24) after the last injection resulting into a total study duration after enrolment of 64 weeks for each participant.

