#### **5.5 Replacements in the Enrolment and Randomisation Lists**

Study participants who withdraw consent, are lost to follow up or are terminated from the vaccination schedule (e.g. because of pregnancy) should not be replaced in the randomisation list. The next consecutive assignment number on the list should be allocated to the next participant. The randomisation lists at each centre will be long enough to allow this. Whilst enrolment is ongoing, every effort will be made to achieve the planned number of 198 participants completing all five immunisation timepoints, and therefore slightly more than 198 may be enrolled.

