## 9.3 Sample size

One hundred and eighty (180) individuals will be randomised to an active product group for the purpose of the analysis, with a further 18 individuals randomly allocated to receive saline for the purpose of blinding the laboratory and clinical staff and to reinforce the message that participants should not consider themselves protected against HIV. There will be two randomisations, the first to compare the three DNA treatment groups, each of which will have approximately 60 participants, and the second to compare two groups, namely MVA-CMDR given with CN54rgp140/GLA-AF and MVA-CMDR alone, each of which will have approximately 90 participants.

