### Statistical assumptions

Alpha will be reduced to 2.5% ( $p=0.025$ ) to adjust for multiple comparisons of the first randomisation, and will be 5% for the second randomised comparison. The following tables illustrate the power to detect a difference in a continuous variable or proportion with 60 or 90 subjects per group, using magnitude of response, and frequency of responders respectively.

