#### **Power to detect a range of differences in a proportion:**

| Increase in absolute difference (control to group of interest) | Power when n=60 per group | Power when n=90 per group |
|----------------------------------------------------------------|---------------------------|---------------------------|
| 40% to 70%                                                     | 86                        | 98                        |
| 40% to 60%                                                     | 48                        | 77                        |
| 50% to 80%                                                     | 89                        | 99                        |
| 50% to 70%                                                     | 50                        | 78                        |

60 participants per group provides adequate power ( $\geq 85\%$ ) to detect a doubling in mean magnitude or to detect a 30% absolute difference in the proportion of responders however the latter is defined. However, there is insufficient power to detect smaller differences, which could still be clinically meaningful. Ninety participants per group also provides adequate power for detecting a 75% increase in the magnitude of immune responses.

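### The responder-rate power table in 9.3 is a normal-approximation calculation, but the planned test is Fisher's exact; at 60 per group power for 40% v 70% is 81%, not 86%

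*Protocol*

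**What the plan says.** Section 9.3 sets out two comparisons: "the first to compare the three DNA treatment groups, each of which will have approximately 60 participants", and a second between MVA with and without the protein boost, "each of which will have approximately 90 participants". Under the heading on statistical assumptions, "Alpha will be reduced to 2.5" per cent for the first randomisation, "and will be 5% for the second randomised comparison".

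An important difference in responder rates is defined as 30 percentage points. The power table then gives, for 60 and 90 per group respectively, 86 and 98 for 40% v 70%, 48 and 77 for 40% v 60%, 89 and 99 for 50% v 80%, and 50 and 78 for 50% v 70%. The text concludes that "60 participants per group provides adequate power", put at 85% or more, for a 30-point difference under any definition of responder. It adds that smaller differences, for which power is insufficient, could still matter clinically.

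The table names no test or formula. The test appears in section 9.5.2: "Proportions will be presented with a confidence interval and groups compared using Fisher's exact test".

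Section 9.3 gives no loss rate. Section 5.5 says that, while enrolment is open, "every effort will be made to achieve the planned number of 198 participants completing all five immunisation timepoints", so slightly more than 198 may be enrolled.

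**The concern.** A power figure belongs to a particular test. Fisher's exact test conditions on both margins, and with 60 per group the attainable significance levels are coarse, so it rejects less often than its nominal level allows. If the table was worked out for a less conservative procedure, it credits the planned analysis with power that it does not have.

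The claim of at least 85% is the protocol's stated justification for 60 per group in the DNA-priming comparison. If it is wrong for the named test, readers are misinformed about the chance of missing an electroporation effect of the size that the protocol itself calls important.

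**Working it through.** **Inputs.** From section 9.3: 60 per group at alpha 0.025 (first randomisation), 90 per group at alpha 0.05 (second), and the four pairs of rates in the table. From section 9.5.2: Fisher's exact test. The protocol does not say whether alpha is one- or two-sided. Two-sided is assumed, because it reproduces the table.

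**Step 1: reproduce the stated figures.** The pooled normal approximation without continuity correction is

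power = Φ{ [ |p1 − p2| − z·√(2·p̄(1 − p̄)/n) ] / √( [p1(1 − p1) + p2(1 − p2)]/n ) }, with p̄ = (p1 + p2)/2.

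For 40% v 70%, n = 60 and alpha 0.025: z = 2.2414 and p̄ = 0.55. Then z·√(2 × 0.55 × 0.45/60) = 0.2036, and √((0.24 + 0.21)/60) = 0.0866. So power = Φ((0.30 − 0.2036)/0.0866) = Φ(1.113) = 86.7%, against 86 stated.

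All eight entries agree within 1 point (table below). With a continuity correction the n = 60 column would read 82.1, 40.6, 85.7 and 42.2 in the protocol's row order, which misses the stated values by 3 to 8 points. The published table is therefore the uncorrected version.

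**Step 2: power of the planned test.** For each pair of responder counts (x, y), take the two-sided Fisher p-value (sum of hypergeometric probabilities no larger than the observed one). Count the pair as a rejection if p ≤ alpha, and sum the product of the two binomial probabilities over the rejection region.

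| Rates | n per group | Stated | Normal approx. | Fisher's exact |
|---|---|---|---|---|
| 40% v 70% | 60 | 86 | 86.7 | 81.4 |
| 40% v 60% | 60 | 48 | 47.9 | 39.4 |
| 50% v 80% | 60 | 89 | 89.8 | 86.5 |
| 50% v 70% | 60 | 50 | 49.8 | 42.7 |
| 40% v 70% | 90 | 98 | 98.6 | 97.7 |
| 40% v 60% | 90 | 77 | 77.0 | 70.6 |
| 50% v 80% | 90 | 99 | 99.1 | 98.7 |
| 50% v 70% | 90 | 78 | 78.7 | 74.9 |

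**Step 3: why the two differ.** Setting p1 = p2 and maximising the rejection probability over the common rate gives a true size for Fisher's test at n = 60 of at most 1.6%, against the nominal 2.5%.

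**Step 4: is 40% v 70% an isolated case?** Other 30-point pairs at n = 60 give Fisher power of 81.4 (30% v 60%), 80.7 (35% v 65%) and 83.8 (45% v 75%). All are below 85.

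**Step 5: what would restore the claim.** Fisher's test first reaches 85% for 40% v 70% at 64 per group (85.6%; at 63 it is 84.5%). At 60 per group, Boschloo's exact unconditional test gives 85.7% for 40% v 70% and 89.8% for 50% v 80%, with maximum size 0.0242.

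**Step 6: sensitivity to losses, as illustration only.** The documents give no loss rate, so the evaluable numbers here are assumptions. For 40% v 70% and 50% v 80%, Fisher power is 81.9% and 84.0% at 57 per group (5% loss), and 77.5% and 81.5% at 54 per group (10% loss). At 57 the first figure does not fall below its value at 60, because exact-test power moves in small jumps with n.

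**The case against.** **The choice of endpoint is still open.** Section 9.5.2 leaves the choice between responder rate and response magnitude, and the detailed methods, to the statistical analysis plan. A Fisher comparison may not end up as the primary analysis. That is fair, but the protocol already names the test to be used if proportions are compared, and it already publishes power for that comparison. The two statements disagree whatever is chosen later.

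**The gap is modest.** This stands. Without losses, both tabulated 30-point rows keep more than 80% power at 60 per group, and at 90 per group they stay near 98% and 99%. The largest falls at n = 60 are in the 20-point rows, which the protocol already describes as underpowered.

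**Fisher's test is valid.** This also stands. It controls type I error and is merely conservative. A reader might infer that it has to be replaced, in the safety analysis of section 9.5.3 as well. The power mismatch does not show that: it concerns the immunogenicity proportions, and correcting the figures is enough.

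**Losses.** A reader might go further and take 78% (10% loss) as the real power, arguing that over-enrolment cannot help. The argument would run that "The enrolment period is planned to be 10 months", about 43.5 weeks, and the fifth immunisation falls at week 40, so with even accrual only (43.5 − 40)/43.5 = 8% would have reached it when enrolment closes. The documents do not support that conclusion:

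- A drop-out is known when it happens, not at week 40. Under the same even accrual, mean time at risk before week 40 at the close of enrolment is (40²/2 + 40 × 3.5)/43.5 = 21.6 weeks, or 54% of 40. With a constant drop-out rate (assumed), about half of the losses could still be made up under section 5.5.
- Sections 7.1.2 and 7.6 keep participants who stop immunisation in view for the primary endpoint visit, and the ITT population in 9.5.1 needs only one immunisation. Stopping early therefore need not mean a missing endpoint.
- No loss rate is stated anywhere.

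**Conclusion.** The point holds for the match between table and test. The proportion table in 9.3 gives the power of an uncorrected normal-approximation test, while 9.5.2 plans Fisher's exact test. At 60 per group the overstatement is about 5 points for 40% v 70%, 2 to 3 points for 50% v 80%, and 7 to 9 points in the 20-point rows. At 90 per group it is under 1 point in the 30-point rows and 3 to 6 points in the 20-point rows.

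The sentence claiming at least 85% is wrong as written, because 40% v 70% gives 81%. It would be too strong to say that every 30-point difference falls short: 50% v 80% still meets the claim at 86.5%.

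The figures rest on two-sided testing, the protocol's own rates and alphas, and full evaluable groups of 60 and 90. No bias, type I error inflation or participant risk is involved.

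**What to change.** In section 9.3, recalculate the proportion table for Fisher's exact test and say that it is for that test: 81, 39, 86.5 and 43 at 60 per group, and 98, 71, 99 and 75 at 90 per group, in the row order 40–70, 40–60, 50–80, 50–70. Replace the claim of at least 85% with about 81% to 87% for the two tabulated 30-point differences, and drop the assertion that it holds under any definition of responder.

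Alternatively, keep the 85% claim for the two tabulated 30-point rows by naming a less conservative exact test, such as Boschloo's, for the immunogenicity proportions in 9.5.2 and stating its power (85.7% and 89.8% at 60 per group). This is optional.

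It would help, but is not essential, to add one line giving power at a plausible evaluable number, marked as an assumption.

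The cost is a recalculated table and a changed sentence. No additional participants are needed. The stated power becomes somewhat less favourable if Fisher's test is kept.

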### Disease/participants studied

198 healthy, HIV uninfected volunteers, 18 to 40 years old who are at low risk of HIV infection will be recruited with 80 from Mbeya and 80 from Dar es Salaam, Tanzania and 38 from Maputo, Mozambique. A minimum of 50 females will be enrolled, and they will be evenly distributed between the three groups.

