### 3 SELECTION OF CENTRES/CLINICIANS

#### 3.1.1 Muhimbili University of Health and Allied Sciences (MUHAS)

MUHAS has established in collaboration with the MNH a dedicated HIV clinic that offers comprehensive HIV care. Additionally, a dedicated HIV vaccine clinical trial unit is in place within MNH premises that is closely linked with the Department of Microbiology/Immunology at MUHAS. This allows for an ethical conduct of HIV vaccine trials by providing an experienced study team, community outreach team, pharmacy expertise, data management capabilities, as well as competent laboratories. The HIV vaccine clinic has built up experience and capacities throughout the conduct of the HIVIS03 trial and the ongoing TaMoVac I study. The clinical and laboratory study team is GCP and GCLP trained and repeat training is performed every other year. Throughout these studies good relationships have been established to a cohort among Police Officers which serves as the basis for the recruitment. Extended community involvement into the general population as a source of recruitment has been established throughout the TaMoVac I. The clinical and laboratory study team is GCP/GCLP trained and repeated training is performed every other year. Operators performing the ELISpot assay have received training and passed an operators validation test which involves running three known samples with low, medium and high IFN-gamma ELISpot reactivity to a peptide pool on three different occasions.

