#### 3.1.2 NIMR-Mbeya Medical Research Center (MMRC)

MMRC had been involved in past HIV vaccine and cohort trials and has established an experienced study clinic, community outreach team, pharmacy and laboratories. MMRC has built up trial experience throughout numerous past and ongoing HIV cohort (HISIS, CODE, RV217) and HIV vaccine trials (RV172, TaMoVac I and RV262). Clinical support is provided throughout close collaboration with the Mbeya Referral Hospital (MRH). The MMRC labs include a clinical laboratory (haematology, clinical chemistry, serology, CD4 count analysis, HIV testing and HIV RNA) as well as an immunological lab which has established FACScanto flow cytometry, ICS and ELISPOT assays throughout various studies. Both labs have been accredited by the College of American Pathologists (CAP) and participate in external QA/QC programs with UKNequas and CAP and follow therefore the highest standard of quality control and validation which is audited and monitored yearly by independent consultants. The MMRC labs have been recognized as one of the national reference laboratories. The clinical and laboratory study team are GCP/GCLP trained and repeat training is performed every other year.

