### 5.2 Randomisation

There will be two randomization steps. During the first step prior to any vaccination, participants will be randomized according to different DNA immunizations (Groups 1, 2 or 3) and according to vaccine or placebo (A or B). During the second step prior to MVA, vaccination participants will be randomized according MVA (Group A1) or MVA plus gp140/GLA (Group A2) boosting maintaining the placebo affiliation (Groups B1 or B2). Randomisation lists will be drawn up under the supervision of [name]. These will be stratified by centre and gender to ensure a balance between the three active groups and matched placebos. The assignment for each subject will be placed in an envelope with a unique sequential number. Six sets of plain envelopes will be prepared, two for each centre (for males and females) and couriered to the Study Pharmacist for that centre who will take the prepared envelopes and put them in a box that is kept under lock.

The pharmacist will randomise participants accepted into the study, after receiving a copy of the participant's signed informed consent from nurse/doctor, by selecting the next consecutive envelope containing the vaccine or placebo assignment in accordance with the generated randomization list. The Pharmacist will make a record of the assignment and study number in a register held under lock. In the case a subject has to be replaced this is noted in the register; their assignment should not be given to the next volunteer to be randomized. The next volunteer should be allocated the next assignment. The Pharmacist will then inform the Study Nurse/Medical Officer at the clinic of the randomization group, I – III of the participant, but will not inform on whether this is vaccine or placebo. The Study Nurse/Medical Officer will record the group assignment in the study record of the participant's file. Procedures for the second randomisation will be similar. In addition to centre and gender, allocation will be stratified on the outcome of the first randomisation.

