### 7.4.1 Cellular responses

The **primary immunogenicity endpoint** will be measured by a standard IFN- $\gamma$  ELISPOT assay using fresh PBMC and pools of overlapping peptides representing Env, Gag and Pol proteins. ELISPOT responses are considered positive if the numbers of spot-forming cells (SFC) are more than four times the background (RPMI medium only) and > 55 SFC per million PBMC (Merck definition). Quality control and exchange of specimens with international laboratories will be performed.

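### Both randomisations are stratified by centre and gender, but section 9.5.2 fixes an unstratified Fisher test and unspecified rank tests; if response levels differ between centres, this gives up power that a centre-stratified analysis would keep.

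*Protocol*

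**What the plan says.** On allocation, Protocol section 5.2 says of the randomisation lists: "These will be stratified by centre and gender to ensure a balance between the three active groups and matched placebos". For the second randomisation it adds: "In addition to centre and gender, allocation will be stratified on the outcome of the first randomisation". Planned recruitment is "80 from Mbeya and 80 from Dar es Salaam, Tanzania and 38 from Maputo, Mozambique" (section 1.1).

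On analysis, section 9.5.2 says "groups compared using Fisher's exact test. Response magnitude will be compared between groups using rank tests", with no mention of centre, gender or strata. The same paragraph leaves the detailed methods, and the choice between responder proportion and magnitude, to the SAP.

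On the assay, section 7.4.1 measures the primary cellular endpoint by "ELISPOT assay using fresh PBMC and pools of overlapping peptides". Section 3.1.1 says of Dar es Salaam: "Operators performing the ELISpot assay have received training and passed an operators validation test". Section 3.1.2 credits Mbeya with "an immunological lab which has established FACScanto flow cytometry, ICS and ELISPOT assays throughout various studies". Section 3.1.3 says the Maputo laboratory was equipped to monitor post-vaccination responses by the same assay. Section 7.4 lists these three laboratories plus Stockholm and WRAIR, without allocating assays among them.

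**The concern.** Stratified allocation holds centre nearly equal across arms, so centre differences cancel from the comparison between arms. An unstratified test still counts them as noise. Its reference distribution is then too wide, its true size falls below nominal, and power is lost.

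Centre could well predict ELISpot results. Fresh cells point to local assay, so centre probably also means laboratory. The source populations differ too: police and prison officers plus the public in Dar es Salaam, urban Mbeya, and a youth clinic in Maputo (section 4.3).

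What is at stake is power for the smaller effects. Section 9.3 itself concedes that power for these is insufficient although they could be clinically meaningful.

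**Working it through.** **Inputs from section 9.3.** SD 0.5 on log10 SFC; 60 per group at alpha 0.025 (first randomisation); 90 per group at alpha 0.05 (second). Two-sided tests are taken because they reproduce the tables. Centre weights are 80:80:38.

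**Step 1: reproduce the plan's power.** Power = Φ(d / [SD·√(2/n)] − z), with z = 2.241 or 1.960.
- Doubling, n = 60: d = log10 2 = 0.301; SE = 0.5·√(2/60) = 0.0913; Φ(3.298 − 2.241) = 85.5%. Stated: 85.
- 50% increase, n = 90: d = 0.176; SE = 0.0745; Φ(2.362 − 1.960) = 65.6%. Stated: 66.

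All 14 cells of the two power tables reproduce within 2 points.

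**Step 2: assumed centre differences.** The documents give none, so a range is used, with total SD held at 0.5. For offsets 0, +0.3 and −0.3 log10:
- mean = 0.3·(80 − 38)/198 = 0.0636
- variance = 0.09·(118/198) − 0.0636² = 0.0496
- share s = 0.0496/0.25, about 20% of total variance.

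Offsets of ±0.15 give a quarter of that, about 5%.

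**Step 3: true size when strata are ignored.** With arms balanced within centres, size is approximately 2·[1 − Φ(z/√(1 − s))]. At s = 20% this is 1.2% against a nominal 2.5% and 2.8% against 5%. Simulated Wilcoxon tests agree (1.3% and 2.8%); stratified by centre they give 2.4% and 4.9%.

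**Step 4: simulated power, Wilcoxon against van Elteren by centre.**

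| Centre offsets | Doubling, n=60, alpha 0.025 | 50% increase, n=90, alpha 0.05 |
|---|---|---|
| none | 83% → 83% | 64% → 64% |
| ±0.15 (s about 5%) | 84% → 85% | 63% → 65% |
| ±0.3 (s about 20%) | 85% → 90% | 64% → 71% |

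Simulation error and the choice of run move these by about a point. With no offsets, stratifying costs 1 point or less. A 75% increase at n = 60, a case the protocol tabulates at 66%, goes from 64% to 73% at ±0.3.

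**Step 5: proportions, 40% v 70%, n = 60, alpha 0.025.**

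| Centre response rates | Fisher | Pearson, unstratified | Cochran-Mantel-Haenszel (CMH) by centre |
|---|---|---|---|
| equal | 82% | 86% | 86% |
| log-odds offsets ±0.5 | 82% | 86% | 88% |
| log-odds offsets ±1 | 84% | 88% | 92% |

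The step from Fisher to Pearson, about 4 points, is Fisher's conservatism. Only the step from Pearson to CMH is due to stratifying: 0, 2 and 4 points. Exact Fisher power for this case is 81.4%, against the stated 86, even with equal centre rates.

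**Step 6: centre alone or centre by gender.** Section 1.1 requires at least 50 women among 198. Assuming they spread over centres in proportion, Maputo has 38·50/198 = 9.6 women. Of these, 9.6·180/198 = 8.7 are on active product, or about 3 per DNA arm. With no centre effect, stratifying by centre and gender together costs about 1.7 points at n = 60 (82.8% to 81.1% for a doubling). No gender effect was modelled.

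**The case against.** Much of the case against is sound.

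- Stratum handling is commonly left to the SAP, which is not at hand, and section 9.5.2 defers detail to it. The wording on rank tests does not exclude a stratified one, since van Elteren is itself a rank test. For magnitude, then, the point is a request to specify. Fisher's test is different: it is named, and an SAP that follows the protocol inherits it.
- The protocol works to limit laboratory differences, through quality control and specimen exchange (7.4.1), operator validation (3.1.1), external quality assurance at Mbeya (3.1.2) and standard procedures in all laboratories (10.2). These may shrink the offsets; nothing shows that they remove them. Offsets of ±0.3 mean a fourfold gap between the extreme centres.
- Local ELISpot is an inference from sections 3.1 and 7.4.1. The laboratory argument does not carry over to the antibody endpoints, which use frozen serum or plasma (7.4.2).

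A reader might infer that power is certainly being lost, that the planned comparisons are invalid, or that the stated power for a doubling fails. The documents support none of these. They give no between-centre variance, the error in size is on the safe side, and the unstratified rank test keeps roughly 82% to 86% power for a doubling at 60 per group across the offsets examined.

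**Conclusion.** The mismatch between a stratified allocation and a named unstratified test is in the text. The consequence is possible inefficiency only. For the rank test the gain from stratifying by centre is about 0 points with no centre differences, 1 to 2 at ±0.15 log10, and 5 to 8 at ±0.3 for the two comparisons in the Step 4 table. This rests on total SD 0.5, arms balanced within centres, and offsets that are assumed. For proportions, part of the apparent gain belongs to replacing Fisher's test rather than to stratifying. Confidence is high that the strata are absent from the named analysis and low about how much power this costs. The change is still worth making, because the possible gain exceeds the possible cost.

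**What to change.** In section 9.5.2, and in the SAP before unblinding, name:
- for responder proportions, a Cochran-Mantel-Haenszel test stratified by centre, reported with a stratified risk difference and its confidence interval;
- for magnitude, the van Elteren (centre-stratified Wilcoxon) test.

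Keep the unstratified Fisher and rank tests as sensitivity analyses. Use centre as the stratum rather than centre by gender, because women in Maputo would form very small cells, smaller still for magnitude, which is restricted to positive responders. State whether the CMH test is the large-sample or an exact version: the simulated version matches the unstratified Pearson test when centre rates are equal, and a continuity-corrected or exact version would give back some of the gain over Fisher.

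The cost is one or two sentences and no new data. The downside is about 1 point of power or less if centres do not differ.
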